### Potential Covariates/Confounds

*BDNF* methylation and protein levels vary by age, sex, and pubertal status (98–101), as well as lifestyle factors including BMI and smoking (101–103); therefore, we are collecting information on these factors at all time points to be investigated as potential covariates. We will also examine the effect of overall bodily injury severity because polytrauma can be a significant confounder in biomarker studies (75, 104).

Pubertal status is measured for children ≥8 years using the self-report Pubertal Development Scale (105). The scale provides a Pubertal Development Score, which shows adequate agreement with direct clinical assessment of Tanner staging (106).

The child's BMI is obtained at each visit from the EMR or study staff.

Parents are given a brief screener measuring the child's exposure to nicotine and tobacco. The screener measures maternal use and secondhand exposure during pregnancy, as well as the child's secondhand exposure. Children 10 and up also complete a brief self-report measure about their own nicotine and tobacco use. They are asked how frequently they have used a variety of nicotine/tobacco products. Children complete the questionnaire on paper while their parents are out of the room and are informed that their responses will be kept private.

The Injury Severity Score (ISS) (107) measures overall bodily injury severity and is obtained from the local trauma registry. The score for injury to the head will be excluded to avoid confounding with TBI severity.

### Data Management

All electronic and paper data storage is IRB and HIPAA compliant through separation of identifiable and deidentified data, storage of paper data, and samples in locked cabinets in locked offices, use of secure servers, and encrypted and password-protected files and computers. Research Electronic Data Capture (REDCap) is used for electronic data storage. REDCap is a web-based platform that allows a common database for data entry and rules for data handling. All data that are entered into REDCap are checked for discrepancies using double verification and error checks.

### Data Reduction, Missing Data, and Attrition

Measures were selected that provide composites or summary indices representing each construct, reducing the need for substantial data reduction. Children will be eligible to remain in the study if at least one acute biosample (CSF, blood, or saliva) is obtained and both primary parent questionnaires (BRIEF-2/P, SDQ) are completed. This will reduce missing data on key variables and retain participants who refuse blood collection or are unable to produce sufficient saliva. In addition, statistical techniques such as mixed models, latent class trajectory analysis, and path analysis will be used, which estimate models based on all available data using maximum likelihood estimation (108). Consistent with previous studies in this population, we conservatively estimate that ~75% of participants will complete the follow-up visits (150 TBI; 75 OI) (2, 4, 5). Our power analyses account for this reduced participant sample size at follow-up.

### Data Analyses

#### Biomarker Analysis

DNA extracted from saliva, blood, and CSF will be processed for methylation analysis. We currently plan to use EpiTect Methyl II PCR assays (Qiagen, Germantown, MD) to assess targeted methylation sites in and around the *BDNF* gene; however, due to rapid changes in technology for this type of data collection, when data collection is to begin, we will evaluate whether this method remains our best choice. We will target a select number of *BDNF* CpG islands for this initial study that showed the strongest correlation between blood and CSF in our preliminary data (109) and show significant correlations between *BDNF* methylation in blood and postmortem prefrontal cortex brain tissue according to the searchable online Blood Brain DNA Methylation Comparison Tool (110). Additional *BDNF* methylation targets may be examined in secondary analyses. The resulting data will estimate the methylation level at each CpG site by beta values (i.e., percent methylation). Beta values range from zero to 1, with zero indicating a null methylated site and 1 indicating a fully methylated site. *M* values will then be calculated and used in statistical analysis. (111, 112) Plasma BDNF protein levels will be measured using an ELISA kit according to the manufacturer's instructions. BDNF ELISA kits are available from several manufacturers (e.g., RayBiotech, R&D Systems). We will select a manufacturer at the time of analysis based on available specifications. For quality control, biosamples will be batch analyzed, assays will include biological duplicates and technical replicates, and data will be evaluated by two individuals blinded to phenotype.

Before our main analyses, we will examine the concordance of *BDNF* methylation across saliva, blood, and CSF and compare the predictive value of epigenetic results across biosample types. Based on these results, we may determine that saliva or blood biosamples are more informative than the other, and these results will guide which biosample(s) are used for measurement of *BDNF* methylation in our primary analyses.

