The brain-derived neurotrophic factor (*BDNF*) gene is an ideal candidate for the first exploratory examination of epigenetic influences on neurobehavioral recovery following pediatric TBI because it is involved in both: (1) the biological response to childhood adversity and (2) neuroplasticity following TBI. BDNF is a well-studied member of the neurotrophin family of growth factors. It is released from neurons both pre- and postsynaptically and mediates apoptosis, neuronal differentiation, outgrowth of neurites, cell survival, and synaptic strengthening (31, 32). Thus, BDNF is intimately involved in brain development, neuroplasticity, and neuronal survival (33, 34), as well as complex cognitive processes, including learning/memory (35, 36) and executive functioning (37–40). A single-nucleotide polymorphism producing a valine-to-methionine substitution at codon 66 (val66met) in the *BDNF* gene is associated with reduced activity-dependent secretion of BDNF (41) and may modify methylation level at this position on the gene (42–44). In addition to other transcriptional and translational regulators (45, 46), *BDNF* gene expression, as is the case with many genes, is regulated in part by DNA methylation, such that higher methylation is associated with lower neuronal synthesis of BDNF (47).

*BDNF* DNA methylation epigenetically encodes the effects of childhood adversity on neurodevelopment. Multiple recent studies show that early adversity produces changes in *BDNF* methylation detectable in the brain and peripheral biosamples in both animal models (48–50) and humans (23, 51–53). Both higher *BDNF* methylation (23, 54) and lower BDNF protein levels (55–60) are associated with worse neurobehavioral outcomes in children with preterm birth, attention-deficit/hyperactivity disorder (ADHD), bipolar disorder, anorexia, and autism spectrum disorder.

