The BDNF pathway is also involved in neural recovery from TBI. BDNF is upregulated in the frontal cortex and the hippocampus after experimental TBI and may mediate recovery processes after brain injury (61–63). In adult clinical studies, BDNF levels in cerebrospinal fluid (CSF) show a sharp spike within 24 h postinjury and steadily decline over 1 week (64, 65), providing evidence for BDNF upregulation and involvement in recovery post-TBI consistent with animal models. BDNF levels during the first week postinjury tend to be comparable in CSF (65) but lower in serum in adults with TBI relative to nonbrain-injured controls (65, 66). Furthermore, acute and chronic BDNF levels in CSF and serum/plasma after TBI in adults predict outcomes, including mortality (65), global outcomes (66, 67), and long-term functional cognition and depression (68, 69). Far fewer studies have examined BDNF levels after pediatric TBI. Initial evidence shows a sharp peak in BDNF levels immediately following injury, followed by subsequent declines (70, 71), similar to that shown in adults. Higher CSF and plasma/serum BDNF levels predicted better global recovery in pediatric TBI studies (71, 72), but to our knowledge, no known studies have examined *BDNF* genetics or epigenetics in association with TBI outcomes in children.

Thus, the overarching goal of our study is to investigate an epigenetic biomarker involved in both childhood adversity and postinjury neuroplasticity to better understand heterogeneity in neurobehavioral outcomes following TBI. Our primary hypothesis is that childhood adversity will be associated with worse neurobehavioral recovery in part through an epigenetically mediated reduction in *BDNF* expression in response to TBI (see Figure 1).

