Aim 1: Examine differences between TBI and OI in *BDNF* methylation and BDNF protein levels over the recovery period. We hypothesize that *BDNF* methylation will be higher, and BDNF protein levels will be lower, in children with TBI relative to OI at all time points, and that *BDNF* methylation will decrease, and BDNF protein levels will increase, in the TBI group over time but will remain relatively stable in the OI group.Aim 2: Characterize trajectory classes of *BDNF* methylation and BDNF protein levels following TBI while controlling for potential demographic, injury, and lifestyle covariates. We hypothesize the presence of at least two *BDNF* methylation trajectory classes and two BDNF protein level trajectory classes representing varying degrees of recovery from TBI. We will explore age, sex, pubertal status, TBI severity, overall injury severity, body mass index (BMI), and smoking as potential covariates.Aim 3: Test the indirect effect of childhood adversity on neurobehavioral recovery following pediatric TBI, as mediated by *BDNF* methylation and BDNF protein level trajectory classes.

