### Biomarker Collection and Processing

CSF is collected by the bedside nurse into a CSF vial and refrigerated until processing within 48 h by the CHP PCTRC. Processing involves separation and aliquoting of supernatant for future protein level analysis and the cell pellet for genetic and epigenetic analysis. Processed samples are stored at −80°C.

Acute blood samples are collected by the child's bedside nurse from his or her IV if patent or via venipuncture with parent and child permission. Chronic blood samples are collected via venipuncture by a PCTRC nurse. Up to 10 cc of blood is collected at each draw into ethylenediaminetetraacetic acid (EDTA) vacuum tubes and refrigerated until processing within 48 h by the PCTRC. Processing involves separation and aliquoting of plasma for future protein level analysis and the buffy coat (leukocytes) for DNA extraction using a simple salting protocol for genetic and epigenetic analysis. Processed samples are stored at −80°C.

Up to 2 ml of saliva is collected by the study staff using Oragene DNA sample collection kits (DNA Genotek, Ontario, Canada). To collect saliva, the child spits into the Oragene collection tube for 2–5 min until liquid saliva reaches the fill line. If the child is unconscious or unable to spit, study staff instead use a sponge to gently swab the child's gums and inner cheeks and then wring the saliva out of the sponge into the collection tube until the fill line is reached. The study staff then close the tube's lid to release the stabilizing liquid and store the sample at ambient temperature until processing. DNA is extracted using the reagents and protocol from the manufacturer.

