##### Aim 2: Characterize trajectory classes of BDNF methylation and BDNF protein levels following TBI while controlling for potential demographic, injury, and lifestyle covariates

We will use latent class trajectory analysis (LCTA) (113) of *BDNF* methylation and protein levels separately, with the goal of identifying clusters of children with TBI who follow similar recovery trajectories. Some of the major benefits of LCTA are identification of distinct classes, simplification of complex data, and identification of adverse trajectories for potential intervention targets. Another strength given our heterogeneous sample is that probability of membership in each latent class is identified based on biomarker values over time as well as scores on significant covariates. Covariates to be tested will include age, sex, pubertal status, TBI severity, overall injury severity, BMI, and smoking. We will examine biomarker distributions to determine the need for transformations (114). Model selection will involve the iterative estimation of the number and shape of trajectory classes and identification of the best fitting model utilizing the following verified fit indices: Bayesian information criterion statistic, model estimation convergence, percentage of population in each subgroup (>10%), minimization of the residual variance statistic, and examination of posterior subgroup classification probabilities (115–117). Although the literature on power analyses for LCTA is limited (117), the power to identify the appropriate number of classes is highly dependent on separation of the trajectories (115). We believe our final sample is sufficient for several reasons: (1) we have a strong theoretical basis for our hypothesis of at least two classes and expect the classes to be relatively distinct; (2) we intend to evaluate different forms of the extracted model using verified fit indices (115); and (3) LCTA with covariates has been successfully applied in smaller TBI samples, *n* = 100–138 (75, 118–120).

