Regarding potential weaknesses, the wide age range and breadth of TBI severity of participants introduces greater heterogeneity than more restrictive age and severity inclusion criteria. Given that this is a single-site exploratory pilot study, however, we chose to be more inclusive to ensure a sufficient sample size for the proposed analyses. The effects of demographic and injury factors will be explored as potential covariates to inform the design of future studies. Similarly, *BDNF* methylation can be affected by other factors that are not measured in our study, including alcohol and drug exposure, diet, and exercise. We would look to consider these factors in future larger studies. Whether methylation in peripheral biosamples provides meaningful information regarding methylation in the brain is an inherent challenge to epigenetic research and remains to be further elucidated. Should the targets examined fail to show correlation of *BDNF* methylation between peripheral biosamples (blood and saliva) and CSF or fail to show associations with childhood adversity and neurobehavioral outcomes, the establishment of the biorepository in this study will allow for many additional epigenetic biomarkers to be explored. Finally, we acknowledge that *BDNF* is only one of many epigenetic pathways potentially influencing recovery. Biomarkers of interest to our research questions and available for subsequent analyses will include additional *BDNF* methylation targets, *BDNF*, neurotransmitter (17, 122) and inflammatory (123) genotypes, and additional biomarkers related to neuroplasticity and inflammation, given their role in both childhood adversity and recovery from TBI.

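### Selecting BDNF methylation targets only by cross-tissue correlation favours CpGs partly set by genotype, and the plan neither screens for genotype nor adjusts for it

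*Protocol article*

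**What the plan says.** All references are to the protocol article.

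- **Target selection (Biomarker Analysis).** The first criterion is "We will target a select number of *BDNF* CpG islands for this initial study that showed the strongest correlation between blood and CSF", judged in preliminary data. The second is that the targets "show significant correlations between *BDNF* methylation in blood and postmortem prefrontal cortex brain tissue", judged with an online tool. No criterion concerns genotype, adversity or change after injury.
- **Genotype (Introduction).** The val66met variant is associated with reduced secretion of BDNF and "may modify methylation level at this position on the gene".
- **Covariates (Aim 2 under Statistical Methods and Power).** "Covariates to be tested will include age, sex, pubertal status, TBI severity, overall injury severity, BMI, and smoking". The statement of aims lists the same seven. Potential Covariates/Confounds does not mention genotype either.
- **Deferral (Strengths and Potential Limitations).** Biomarkers "available for subsequent analyses will include additional *BDNF* methylation targets, *BDNF*, neurotransmitter (17, 122) and inflammatory (123) genotypes".
- **Available material (Biomarker Collection and Processing).** The leukocyte layer is kept "for DNA extraction using a simple salting protocol for genetic and epigenetic analysis".
- **Hypothesis (Introduction).** Adversity is thought to act in part through an "epigenetically mediated reduction in *BDNF* expression in response to TBI". Aim 1 expects methylation in the TBI group to fall over the year.

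**The concern.** The hypothesis needs a methylation measure that adversity can shift before injury and that can change after it. The selection rule asks for something else: that children who are high in blood are also high in CSF and in cortex. A responsive site can meet that test. So can a site where a DNA variant sets the level, because the variant is identical in all of a child's tissues. Nothing later in the plan separates the two kinds of site.

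Three things are at stake if a genotype-influenced site is chosen.

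- **Power.** Such a site has less to show in the Aim 1 group-by-time interaction. Its fixed between-child variance also dilutes the Aim 3 paths.
- **Classes.** The Aim 2 trajectory classes can partly be genotype groups, and these classes are the Aim 3 mediators.
- **Confounding.** By the article's own account val66met may affect both methylation and BDNF secretion. An unadjusted methylation-to-protein path could then be read as epigenetic when part of it is genetic.

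**Working it through.** No sample size or power figure in the article depends on the selection rule, so there is none to reproduce for this point. The article's power statements give the background.

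**1. Background power.**
- Aim 1 inputs from the article: partial η² = 0.01, correlation 0.5, three time points, and 150 + 75 = 225 children. Then f² = 0.01/0.99 = 0.0101 and λ = 0.0101 × 225 × 3/(1 − 0.5) = 13.6. With 2 and 446 degrees of freedom, power is 0.92, consistent with the stated 0.8 or more.
- Aim 3: the article gives no numeric path size. With both paths assumed to be 0.26 and N = 150, a joint-significance simulation gives 0.77, close to the stated 0.8.

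**2. Worst case: one CpG destroyed by a variant.** All inputs are assumed: methylation of the intact allele m = 60–90%, variant frequency p = 5–40%, non-genetic SD 3–6 percentage points, and correlation of 0.2 across tissues for the non-genetic part.
- Genotype variance = (m/2)² × 2p(1 − p). Non-genetic variance = SD² × (1 − p)².
- Low end (0.60, 0.05, 0.06): 0.00855 and 0.00325. The genotype share is 0.00855/0.01180 = 72%. Cross-tissue correlation = 0.72 + 0.2 × 0.28 = 0.78.
- High end (0.90, 0.40, 0.03): 0.0972 and 0.00032. Share and correlation both exceed 99%.

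**3. The same variant within an island average.** Assume 10 CpGs with one affected, and an SD of the island mean of 3–6 points. Genotype variance is divided by 10² = 100.
- Low end: 0.0000855/(0.0000855 + 0.0036) = 2%.
- High end: 0.000972/(0.000972 + 0.0009) = 52%.

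**4. What ranking by correlation selects.** Assume 60 candidate sites, with the top 5 taken on a correlation estimated from 20 people. The true correlation is the genotype share plus the shared responsive share.

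| Setting | Genotype share, all → selected | Responsive share, all → selected | Genotype as part of shared variance, all → selected |
|---|---|---|---|
| 1 | 0.10 → 0.13 | 0.20 → 0.29 | 0.33 → 0.30 |
| 2 | 0.20 → 0.30 | 0.20 → 0.30 | 0.50 → 0.50 |
| 3 | 0.30 → 0.50 | 0.15 → 0.21 | 0.67 → 0.70 |
| 4 | 0.40 → 0.72 | 0.10 → 0.13 | 0.80 → 0.84 |

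The genotype share rises in every setting, and so does the responsive share. The ratio between them barely moves, so the rule enriches both and separates neither. (The pre-selection ratio is the genotype share divided by the sum of the two shares.)

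**5. Cost in Aim 3.** Let q be the share of methylation variance that is fixed genotype, unrelated to adversity and outcome. Again N = 150 and both paths are 0.26.

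| q | Power, unadjusted |
|---|---|
| 0 | 0.77 |
| 0.10 | 0.70 |
| 0.25 | 0.57 |
| 0.50 | 0.33 |
| 0.75 | 0.11 |
| 0.90 | 0.02 |

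With genotype as a covariate, power is 0.76–0.77 at every q. The simulation uses a continuous mediator and assumes that the covariate captures all of the genotype share. The plan uses class membership as mediator, so these figures show direction and rough size only.

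**6. Aim 1.** No size was computed. Variance that is constant within a child largely cancels from the group-by-time contrast. The loss there comes from a site that changes little, while group comparisons at single time points also carry the added variance.

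**7. Aim 2 class size.** The plan looks for classes above 10%. Carriers make up 1 − (1 − p)², which is 9.75% at p = 5% and passes 10% just above that. Homozygotes (p²) pass 10% only above p of about 32%. A carrier class could meet the criterion over most of the assumed range; three genotype classes could do so only near its top.

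**The case against.** The strongest reply is that the premise cannot be checked. The article does not name the chosen islands or place codon 66 in one of them, and it gives no genotype share of methylation variance. It says only that val66met may modify methylation. That stands: the documents do not show that a genotype-driven site was chosen.

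It can also be said that responsive sites pass the filter too. The Introduction cites adversity-related BDNF methylation changes detectable in both brain and peripheral samples, and the selection check agrees. This stands as well.

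A third reply is that screening CpGs for variants is laboratory detail that an article leaves out, and that deferring genotype in a declared exploratory pilot is disclosed. This stands only in part. The article does more than stay silent: it fixes the selection criteria, lists the covariates and assigns genotype to later work. Its limitations discuss targets failing to correlate across tissues, but not that a good correlation may come from genotype.

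A reader might infer something stronger: that the assay will measure a DNA variant instead of methylation, and that Aim 3 will then report false mediation of adversity. The documents do not support this. If adversity cannot move a site, the adversity-to-methylation path is absent and the indirect effect tends to null, unless genotype is itself related to adversity.

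**Conclusion.** The point holds as a weakness in a stated rule. Selection by cross-tissue correlation alone favours sites with a genotype component and cannot separate them from the responsive sites that the hypothesis needs. The article itself names a relevant variant, then neither screens nor adjusts for it.

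The size is conditional. The 72% to over 99% genotype share is a worst case for a single CpG destroyed by a variant. For a 10-CpG average the same inputs give about 2% to 52%. Genotype dominates the selected sites only where it was already the larger source of shared variance. If it makes up 25–50% of the chosen measure, Aim 3 power falls from 0.77 to between 0.57 and 0.33. All of these figures rest on assumed allele frequencies, variances and path sizes.

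The expected harm is lost power in Aims 1 and 3, classes that partly reflect genotype, and a methylation-to-protein path open to confounding by val66met. The selection rule does not affect the protein measurement itself.

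**What to change.** Add two conditions to the selection rule in Biomarker Analysis.

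1. Before ranking by cross-tissue correlation, exclude any CpG at, created by or removed by a known common variant, starting with val66met. If the final platform reports only a regional value, apply the check to the CpGs that the region covers.
2. Drop sites whose methylation clusters at zero, half and full.

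The preliminary ranking appears to exist already, so this means reapplying it to the reduced list. The assay is not yet final, which leaves room to do so.

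Optionally, genotype val66met in the DNA already extracted and adjust for it in Aims 2 and 3 (methylation, protein and outcome equations) as a sensitivity analysis.

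The exclusion costs wording and perhaps a few targets. The optional step needs one genotype assay on stored DNA, brought forward from the later analyses already foreseen.

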#### Statistical Methods and Power

##### Aim 1: Examine differences between TBI and OI in BDNF methylation and BDNF protein levels over the recovery period

Unadjusted *BDNF* methylation and protein levels will be compared between TBI and OI groups using mixed effects analysis of variance (ANOVA; time as within effect; group as between effect). Mixed effects ANOVA allows for the modeling of effects on continuous outcomes (BDNF methylation and protein levels), is flexible with missing data, and provides explicit estimation of between group and within group variance. We will use appropriate transformations if normality is violated. We expect a significant group × time interaction and group differences at each time point. Alpha will be set at 0.05, and we will adjust for multiple comparisons using Bonferroni corrections. We expect sufficient power (≥0.8) to detect even a small interaction effect (partial η^2^ = 0.01) assuming correlation of 0.5 between repeated measures (G^*^Power 3.1.9.2).

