##### Aim 3: Test the indirect effect of childhood adversity on neurobehavioral recovery following pediatric TBI, as mediated by BDNF methylation and BDNF protein level trajectory classes

We will conduct path analysis to test the theoretical model shown in Figure 2 within the TBI group. The theoretical model represents the relation among constructs rather than specific measures to allow for fluidity in our approach. For example, we will examine this model for each of the four primary measures of neurobehavioral outcome (NIHTB-CB, BRIEF-2/P, SDQ, Vineland-3). The specific biosamples used for *BDNF* methylation will be informed by preliminary analyses (see *Biomarker Analysis*). Path analysis enables a graphical representation of complex relationships, can explore direct and indirect effects among the variables (e.g., mediation), and infer causal directionality between effects. *BDNF* methylation and protein level trajectory class adjusted for covariates (Aim 2) will be tested as categorical mediators. Neurobehavioral recovery on each outcome will be modeled controlling for premorbid functioning (with the exception of NIHTB-CB). We estimated sample size requirements to adequately power the three single mediator models that would comprise our double-mediator model, as current guidelines on sample size for double mediator models are limited. The power of a single mediator model depends on the effect of the independent variable (IV) on the mediator and the effect of the mediator on the DV, controlling for the IV. Using Cohen's effect size criteria, we expect to have sufficient power (≥0.8) if both effects are at least “halfway” (between small and medium effects) (121). However, we would only need 115 participants if one effect is “halfway” and the other is medium. Thus, our final sample is conservative.

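### Predictive value, compared in the study's own children, helps choose the tissue for the Aim 3 methylation mediator, and nothing corrects for that choice

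*Protocol article*

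**What the plan says.** The Biomarker Analysis section describes a step before the main analyses. The team will examine how well methylation agrees across saliva, blood and CSF, and will also "compare the predictive value of epigenetic results across biosample types". It adds that "we may determine that saliva or blood biosamples are more informative than the other" and that "these results will guide which biosample(s) are used for measurement of *BDNF* methylation in our primary analyses".

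The Aim 3 section repeats the link: "The specific biosamples used for *BDNF* methylation will be informed by preliminary analyses". It also says that "we will examine this model for each of the four primary measures of neurobehavioral outcome".

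The only statement on alpha and multiplicity is under Aim 1: "Alpha will be set at 0.05, and we will adjust for multiple comparisons using Bonferroni corrections". It does not mention the choice of tissue, and the Aim 3 section gives no alpha. No separate sample, cross-validation or adjustment for the choice is described. The earlier preliminary data cited in the Biomarker Analysis section serve to pick CpG islands, not the tissue.

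**The concern.** Two criteria feed the choice. Agreement between tissues uses no outcome data and does no harm to later tests. Predictive value is different. If it means how well methylation predicts neurobehavioral outcome, the tissue that looks better partly by chance becomes the mediator, and the same children then supply the test of that mediator. The nominal error rate no longer holds, and the estimated methylation-to-outcome path is pushed away from zero.

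The reading is an inference, but the article points to it. The Study Overview lists biomarkers among the hypothesized predictors of neurobehavioral recovery, and the limitations section judges targets partly by their association with adversity and neurobehavioral outcome.

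The stake is mainly in planning. The Introduction says that this pilot will guide the design of a larger multisite study. An overestimated path would make that study too small.

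**Working it through.** **Inputs from the article.** Two candidate tissues, saliva and blood (Biomarker Analysis; CSF exists only in a small subsample). 150 children with TBI and 75 with OI at follow-up (Data Reduction, Missing Data, and Attrition). Four primary outcomes (Aim 3). Alpha 0.05 (Aim 1 only).

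**Assumptions, not in the article.** Nominal two-sided 0.05 for Aim 3. Correlation ρ between the saliva and blood test statistics, taken from 0 to 0.95. Standardized associations of 0.10 and 0.26, for illustration.

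**1. The plan's own figure.** The only power figure with full inputs is Aim 1: partial η² = 0.01, correlation 0.5, three time points. With λ = f²·N·m/(1 − r), f² = 0.01/0.99 and N = 225: λ = 0.0101 × 225 × 3/0.5 = 13.64 on 2 and 446 degrees of freedom. Power is 0.92, so the stated 0.8 or more reproduces. The tissue choice does not alter this figure.

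**2. Methylation-to-outcome path, selection on the tested statistic.** The error rate is P(max(|z₁|, |z₂|) > 1.96) under the null. For ρ = 0 it is 1 − 0.95² = 0.0975. The other values come from the bivariate normal.

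| ρ | 0 | 0.5 | 0.7 | 0.8 | 0.9 | 0.95 |
|---|---|---|---|---|---|---|
| error rate | 0.098 | 0.091 | 0.083 | 0.078 | 0.070 | 0.065 |

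**3. Selection on a related statistic.** If the selection statistic correlates 0.5 with the tested one, the error rate is 0.065 (ρ = 0.5) or 0.060 (ρ = 0.8). If the two are independent, it stays at 0.05.

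**4. Indirect effect, joint-significance test.** The error rate is roughly the power of the adversity-to-methylation path times the rate in step 2.
- That path almost always significant: simulation at n = 150 gives 0.095, 0.090 and 0.077 at ρ = 0, 0.5 and 0.8, against about 0.05 with a fixed tissue.
- That path at 80% power: 0.8 × 0.098 = 0.078 at ρ = 0 and 0.8 × 0.070 = 0.056 at ρ = 0.9.
- Both paths null: 0.05 × 0.098 = 0.005 at ρ = 0, so selection does no damage there.

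**5. Size of the estimate at n = 150.** Average estimate from the better-looking tissue, when both have the same true association:

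| true value | ρ = 0 | ρ = 0.5 | ρ = 0.8 |
|---|---|---|---|
| 0.26 | 0.306 (+18%) | 0.293 (+13%) | 0.281 (+8%) |
| 0.10 | 0.142 (+42%) | 0.128 (+28%) | 0.117 (+17%) |

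These also assume selection on the estimated association itself.

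**The case against.** **A reader might infer that all three aims are compromised.** The text does not support that.
- Aim 1 compares TBI with OI, so choosing the tissue by outcome prediction distorts it only if the selection measure tracks group differences.
- Aim 2 selects classes by fit indices and tests no outcome association.
- BDNF protein is measured in plasma, so no tissue is chosen for it.

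**A reader might also take an error rate near 0.09 as the expected figure, separately for each outcome and CpG target.** It is an upper bound. The article reads as one choice for the primary analyses, not a new one for each outcome. The Aim 3 mediator is a covariate-adjusted trajectory class, with premorbid function controlled for three of the four outcomes. A preliminary comparison need not use that statistic.

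**The wording is loose.** Predictive value is undefined, the text says only that one tissue may prove more informative, and the plural allowed for biosamples leaves room to keep both. This lowers the certainty. It does not remove the problem, because no rule says how two tissues would be combined or adjusted for.

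**The study is an exploratory pilot, and an unseen analysis plan could hold a locked rule.** The label lowers the consequence but not the bias, and the article still names a primary hypothesis and primary analyses. Nor is this simply a detail left to another document: the article itself names predictive value as a basis for the choice.

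**Conclusion.** The point holds for the methylation mediator in Aim 3, and should be corrected. Followed as written, the plan lets the tissue be picked partly on the association that Aim 3 then tests in the same children.

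The error rate of the methylation-to-outcome path becomes at most 0.065 to 0.098 instead of 0.05, and about 0.06 when selection and test are only moderately related. The indirect effect is less exposed unless the adversity path is nearly always significant. Where a true association exists, its estimate is too large, proportionately more so when the association is small.

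This rests on three assumptions: predictive value refers to neurobehavioral outcome, Aim 3 is tested at 0.05, and a single tissue is carried forward. Confidence is moderate because the article fixes none of the three.

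**What to change.** State in the Biomarker Analysis section that the tissue is chosen only on criteria blind to outcome, adversity and injury group: concordance across biosamples, assay success, and completeness over the three visits. Lock the choice before biomarker data are linked to outcomes. Report the predictive-value comparison afterwards, as a secondary analysis. Refer to this rule from Aim 3.

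Alternatively, analyse both tissues in the primary analysis at half the alpha each (0.025 if the nominal level is 0.05), which holds the error rate across the two tissues at 0.05 or less.

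**Cost.** A few sentences and no new data.
- The blind rule may not pick the best predictor in this sample. Concordance with CSF rests on a small acute subsample with a drain, so it cannot be checked in the OI group or at 6 and 12 months. Assay success and completeness may have to carry much of the decision.
- Splitting alpha is cheap for Aim 1: power at N = 225 falls from 0.92 to 0.87. It costs more for Aim 3. With both paths at the illustrative 0.26 and n = 150, the expected z is 0.26 × √150 = 3.18. Power per path is Φ(3.18 − 1.96) = 0.89 at 0.05 and Φ(3.18 − 2.24) = 0.83 at 0.025. Joint power for one given tissue therefore falls from about 0.89² = 0.79 to about 0.83² = 0.69, partly offset by having two tissues in which to find the effect.
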